### Follow-up

All patients will be followed actively for 2 years (Figs. 2 and 3) with evaluation at 3, 6, 12, and 24 months from the day of surgery (and randomization). Data on complications including revision will be extracted from the hospital database and patient records after 10 years.

**Fig. 2 Fig2:**
[figure not shown]
SPIRIT figure. Schedule of enrolment, interventions, and assessments of the 56 RSA patients

**Fig. 3 Fig3:**
[figure not shown]
SPIRIT figure. Schedule of enrolment, interventions, and assessments of the 66 patients who are not a part of the RSA study

### Protocol violations, patient drop-out, and revision

If a stemless shoulder arthroplasty during the operation is regarded impossible to insert by the surgeon, the operation can be converted to either cemented or uncemented stemmed total shoulder arthroplasty or cemented or uncemented reversed shoulder arthroplasty. The uncemented stemmed shoulder arthroplasty can be converted to either cemented stemmed total shoulder arthroplasty or cemented reversed shoulder arthroplasty. The patient will be excluded according to the exclusion criteria, and the conversion will be recorded. If the conversion is performed after the randomization, then the patient will be excluded from the RSA and DXA analysis but included in the analysis of the functional outcome and the patient-reported outcome (intention-to-treat).

Patients who drop-out of the trial will be recorded, and the reason for drop-out will be noted. The patient will be included in the final mixed effects model analysis. Drop-outs before the 3-month evaluation cannot be included in the analysis. In addition, a sensitivity analysis will be carried out at the end of the study to assess the impact of missing data on the overall trial results. Patients who do not comply with rehabilitation will be recorded.

If a revision arthroplasty is needed, the reason and the new arthroplasty type are recorded. If possible, the patient is evaluated using RSA, DXA, clinical outcome, and patient-reported outcome prior to the revision procedure. The patient will remain in the study, and they are included in the 2-year analysis with their latest follow-up.

Major protocol modifications will be communicated to all investigators and trial registries immediately.

### Statistics

The nature of data is evaluated before the analysis. The between-group differences are expected to be analyzed with independent *t* test (Student *t* test). If the assumption of normal distribution is violated, then data will be analyzed with non-parametric tests. We do not expect the RSA data to be normal distributed. These data will be analyzed with non-parametric analysis using the Friedmann test for migration over time and the Mann-Whitney *U* test for between-group differences. We expect the DXA data to be normally distributed and changes over time will be evaluated by a parametric analysis using a paired *t* test. Potential between-group differences in BMD changes will be analyzed with independent *t* test (Student *t* test). In addition, due to the nature of repeated measures in this study, we intend to analyze the overall results according to a mixed effects model [45]. The difference between pre- and postoperative scores is expected to be analyzed as a secondary endpoint with parametric analysis using a paired *t* test. Since the two primary endpoints are distinct, multiple testing adjustments will not be performed.

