The aim of this study is to compare the Comprehensive Nano stemless total shoulder arthroplasty (intervention group) with the Comprehensive stemmed total shoulder arthroplasty (control group). Our hypotheses are:
The Comprehensive Nano stemless total shoulder arthroplasty will migrate more than the Comprehensive stemmed total shoulder arthroplasty.The Comprehensive Nano stemless total shoulder arthroplasty will have a superior functional outcome compared with the Comprehensive stemmed total shoulder arthroplasty.

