### Outcome measures

#### Primary radiological outcome

##### Magnitude of migration of the humeral component assessed by MB-RSA

The MB-RSA will be performed according to the guidelines by Valstar and Colleagues [15]. RSA is used to measure humeral component migration. Fifty-six patients will be included in this part of the study. Maximum total point motion (MTPM) after 2 years compared to the baseline value will be used as the primary RSA effect parameter. The precision of RSA will be evaluated by at least 12 double examinations. RSA is performed using a uniplanar RSA arrangement (UmRSA®-Calibration Cage No 43 (hip, spine, and shoulder)). The analysis of x-rays will be performed using the MB-RSA commercial software (RSAcore, Department of Orthopedics, Leiden University Medical Center, Leiden, The Netherlands), available at Skaane University Hospital, Lund Sweden, where analyses of RSA-x-rays will be performed using a well-established research cooperation with consultant orthopedic surgeon, PhD, [name]. The precise set-up for the RSA arrangement (e.g., various distances and the degree between the 2 x-ray tubes) will be determined from a small phantom study and measurements of the 6 pilot patients (3 with each of the 2 types of implants). In addition, the pattern of migration of the humeral component assessed by MB-RSA will be presented using descriptive statistics, but without the performance of statistical tests.

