#### Sample size calculation RSA

Sample size calculation for RSA (maximum total point motion (MTPM) after 2 years will be used as primary RSA effect parameter) with an expected standard deviation (SD) of 0.4 mm, a minimally clinically important difference of 0.4 mm, a significance level at 5%, and a power of 0.90 resulted in 22 participants in each group [46] (56 participants with allowance for 20% drop-out). We intend to include 28 participants in each group. However, the study entails a risk of drop-out and unwillingness to participate, but according to the power calculation, we would be satisfied with a minimum of 22 participants in each group. The estimation of SD = 0.4 mm is extrapolated from a study of migration of the resurfacing arthroplasty [34].

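### The only test named for RSA migration over time is a Friedman test, which uses complete series only and cannot compare the implants' time courses; the mixed model is not said to cover RSA

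*Protocol article*

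**What the plan says.** All references are to the protocol article.

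- **Hypothesis (Background).** The first hypothesis is a difference between arms: "The Comprehensive Nano stemless total shoulder arthroplasty will migrate more than the Comprehensive stemmed total shoulder arthroplasty".
- **Primary RSA measure (Primary radiological outcome).** It is a single time point: "Maximum total point motion (MTPM) after 2 years compared to the baseline value will be used as the primary RSA effect parameter". The same section says that the pattern of migration "will be presented using descriptive statistics, but without the performance of statistical tests".
- **RSA tests (Statistics).** One sentence assigns two tests. For the time course: "These data will be analyzed with non-parametric analysis using the Friedmann test for migration over time". For the arms: "and the Mann-Whitney *U* test for between-group differences". The sentence before it says that RSA data are not expected to be normal.
- **Repeated measures (Statistics).** After the DXA tests the article adds: "due to the nature of repeated measures in this study, we intend to analyze the overall results according to a mixed effects model". It names no outcome, scale or model terms.
- **Drop-outs (Protocol violations, patient drop-out, and revision).** Patients who leave after the 3-month evaluation stay in the mixed model. Revised patients enter the 2-year analysis with their latest follow-up. A missing-data sensitivity analysis is planned.
- **RSA sample size.** The calculation gives 22 per group, recruited as "56 participants with allowance for 20% drop-out".

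**The concern.** The Background justifies serial RSA by the link between continued migration after the first year and later loosening. The Discussion expects RSA to predict how both implants will perform in the long term. A reader will therefore want to know whether the two components settle or keep moving in the same way.

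The test named for that question has two limits:

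- In its standard form it needs a complete block per patient. One missed RSA visit removes the patient from this analysis.
- It is a within-patient test with no arm term. Pooled over both arms, it asks only whether MTPM changes over time. Run in each arm separately, it gives two p values and no comparison between them.

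The mixed model would remove both limits, but the article does not connect it to RSA. Read literally, the plan reports Friedman as the RSA time analysis. At stake are the efficiency and usefulness of a secondary analysis.

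**Working it through.** **1. The plan's own figure.** Inputs from Sample size calculation RSA: SD 0.4 mm, difference 0.4 mm, significance level 5%, power 0.90. Sidedness is not stated; two-sided is taken because it reproduces the figure (one-sided gives 18).

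n per arm = 2 × (1.960 + 1.282)² × (0.4/0.4)² = 21.02, rounded up to 22.

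With 20% drop-out: 22 / 0.8 = 27.5, rounded up to 28 per arm, 56 in total. The stated figures reproduce.

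**2. Is the primary comparison affected?** It uses the 2-year value only. The t test has power 0.900 at 22 per arm and 0.957 at 28. Mann-Whitney power, simulated with 20,000 runs:

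| Data | 22 per arm | 28 per arm |
|---|---|---|
| Normal, SD 0.4, shift 0.4 | 0.885 | 0.946 |
| Lognormal scaled to SD 0.4, shift 0.4 (log-SD 0.6 assumed) | 0.977 | 0.994 |

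The first hypothesis therefore has a planned test with about the intended power.

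**3. What the Friedman test can see.** It ranks each patient's visits against that patient's other visits. In a simulated set of 56 patients and four visits, the statistic was 3.364. After 0.4 mm was added to every visit of 28 patients it was again 3.364, because no within-patient rank changes. A constant difference between arms is invisible to the test. A difference in shape would be averaged into the pooled statistic, with nothing to attribute it to arm.

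**4. Patients with complete series.** The article gives no missingness rate per visit. The RSA schedule is in a figure that is not shown, so RSA at 3, 6, 12 and 24 months is an assumption taken from the Follow-up section. With a share q missing independently at each visit, complete series = 56 × (1 − q)⁴ and 2-year values = 56 × (1 − q).

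| q (assumed) | Complete series | 2-year value present | Difference |
|---|---|---|---|
| 2% | 51.7 | 54.9 | 3.2 |
| 5% | 45.6 | 53.2 | 7.6 |
| 10% | 36.7 | 50.4 | 13.7 |

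The last column counts patients who have the primary endpoint but would be left out of the Friedman test.

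A different assumption takes the planned 20% drop-out as lost by 2 years: 56 × 0.8 = 44.8. A further 5% or 10% missing at each of three interim visits leaves 44.8 × 0.95³ = 38.4 or 44.8 × 0.9³ = 32.7.

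**5. Does the mixed model close the gap?** The text first sends RSA to non-parametric tests because non-normality is expected, and then adds the mixed model for the results as a whole. Nothing excludes RSA and nothing includes it. No scale is given on which a model for skewed, positive MTPM would be fitted.

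**The case against.** The strongest objection is that the plan already covers what matters. The sentence naming the Friedman test goes on to name the Mann-Whitney U test for the arms. The mixed model is introduced because of the repeated measures, and its terms and scale are details that an article may leave to the full protocol or SAP. This stands in large part. The missing model terms are not themselves a fault. What remains is that the article does fix a test for the RSA time course, and that this test is a poor choice beside the model it already plans.

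It can also be said that continued migration is a question within each implant, which a within-patient test addresses. That is fair for the Background. The Discussion, however, speaks of predicting results for both arthroplasties, and an overall test across visits does not show how their courses differ.

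Three stronger readings are tempting, and the documents do not support them:

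- **The first hypothesis cannot be tested.** It is tested on 2-year MTPM by the Mann-Whitney test (steps 1 and 2).
- **Patients with a missed visit lose all their data.** A missed interim visit does not remove anyone from the 2-year test. Drop-outs after 3 months stay in the mixed model, and revised patients contribute their latest follow-up.
- **The Friedman test will mislead.** If the reference examination, where MTPM is zero by definition, were counted as a time point, the test would reject even without migration. If the arms were judged by which one had p below 0.05, two identical arms with power p each would disagree with probability 2p(1 − p), at most 50%. The article states neither practice.

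The descriptive-only statement about the pattern of migration is not a certain contradiction either, since pattern may mean something other than the time course of MTPM.

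**Conclusion.** The point holds as an improvement to a secondary analysis. The Statistics section gives RSA migration over time to a test that, in its standard form, drops incomplete series and carries no between-arm information. It leaves unsaid whether the better-suited mixed model applies to RSA. The properties of the test do not depend on any assumption about this trial.

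The size does. About 52, 46 or 37 of 56 complete series follow from assumed missingness of 2%, 5% or 10% per visit, independence between visits, and four RSA visits. Any claim of bias from selective drop-out would further need an assumed drop-out mechanism, effect and spread, so none is made here. The primary RSA test, its power and the figure of 56 do not change.

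**What to change.** In the Statistics section, replace the Friedman test, or make it supportive, with the mixed model already planned:

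- Outcome: log-transformed MTPM at all postoperative RSA visits, leaving out the zero reference examination.
- Terms: arm, visit, arm-by-visit and a patient random effect, using every available RSA examination.
- Report: the between-arm ratio with 95% CI at each visit.

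Keep the 2-year Mann-Whitney test as the primary RSA analysis. In Primary radiological outcome, align the statement that the migration pattern is shown without tests with whatever the Statistics section then says.

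The cost is a few sentences and a little more analysis work. The downside is a log-scale assumption, which needs a residual check because MTPM is positive and skewed. Sample size and data collection stay as they are.

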#### Sample size calculation RSA

Sample size calculation for RSA (maximum total point motion (MTPM) after 2 years will be used as primary RSA effect parameter) with an expected standard deviation (SD) of 0.4 mm, a minimally clinically important difference of 0.4 mm, a significance level at 5%, and a power of 0.90 resulted in 22 participants in each group [46] (56 participants with allowance for 20% drop-out). We intend to include 28 participants in each group. However, the study entails a risk of drop-out and unwillingness to participate, but according to the power calculation, we would be satisfied with a minimum of 22 participants in each group. The estimation of SD = 0.4 mm is extrapolated from a study of migration of the resurfacing arthroplasty [34].

#### Sample size calculation WOOS

With a standard deviation of WOOS of 15 (15% of a maximum score), a difference of 10 (10% of a maximum score), a significance level of 5%, and a power of 0.90, 48 patients are needed in each group resulting in a study population with 122 participants [46] (allowing for 20% drop-out). No minimally clinically important difference of the WOOS score has ever been reported. Therefore, it is important to mention that the use of 10 points in this study is an arbitrary value.

Data on RSA and DXA will be analyzed at the end of follow-up for 56 patients. We have chosen not to perform a 1-year formalized interim analysis, but an external independent assessor from another hospital will once a year get an update on the study and review the results in a confidential manner. In this way, the scientific validity of the study will be improved.

## Discussion

Apart from the humeral component, the two groups are treated alike. Today, the Comprehensive Nano stemless humeral component and the uncemented Comprehensive stemmed humeral component are considered equal in the treatment of osteoarthritis [47].

We intend to decrease the risk of selection bias through block randomization stratified for age and gender. Through sample size calculation and adding 20% to the result, we compensate for drop-outs and attempt to avoid type II errors (when the null hypothesis is false but fails to be rejected).

The patients in both groups will follow the standard rehabilitation program supervised by a physiotherapist, and furthermore, the surgical approach and technique will follow the standard procedures and be equal in the two groups. This leads to a high external validity of the study. The standard treatment at our department includes a follow-up examination at 3 months. The participating patients will have additional follow-up examinations at 6 months and at 1 and 2 years. Besides being time consuming, this may maintain the patients in a role of being ill. However, the patients will also have the advantage of feeling secure and any uncertainty or problems can be addressed more easily.

With this study, all patients are at risk of being treated with a component that subsequent analyses will deem inferior. This is implicit in the study design, but there is nothing a priori to suggest which technique is the better.

This is a single-center study with all operations being carried out by one of six highly experienced shoulder surgeons. Therefore, the results of the study can only be transferred directly to patients operated by surgeons with the same skills. Thus, we acknowledge that this nature of the study entails a risk of less generalizability.

The patients will not be blinded to their randomization allocation. This would be very difficult in Denmark, as patients have access to their records electronically. However, this is not expected to be of great significance as the patients hardly have an expectation of one of the prostheses to be the superior. Furthermore, it is not possible to blind the outcome assessor as it is the same person analyzing the RSA and DXA, in which one must necessarily have access to the radiographs. However, this is not expected to be of any significance to the second primary outcome, since this is a patient-reported outcome which is completed by the patient independently of the outcome assessor. In addition, the final analyses will be carried out by a blinded statistician associated with the trial.

In a study based on data from the Nordic Arthroplasty Register Association [47], the total stemless shoulder arthroplasty and the total stemmed shoulder arthroplasty appear to have comparable short-time survival. However, it is not known whether they continue to perform equally. Ryd et al. [18] and Kärrholm et al. [48] both found a relationship between short-term RSA results and future loosening of prostheses. They found that already 1-year postoperative RSA can be used to identify prostheses at risk of future loosening. Therefore, the use of RSA in this study will enable us to predict the long-term results of the two arthroplasties.

The main value of the study is new knowledge about the best treatment option for end-stage osteoarthritis. This can be of value to future patients with end-stage osteoarthritis where shoulder arthroplasty is considered.

### Trial status

Version 1.4, October 10, 2019.

Start of inclusion: March 1, 2020.

Finnish date of recruitment to the first part of the study (RSA and DXA): February 28, 2021.

Finnish date of recruitment of all 122 patients: March 31, 2022.

Finnish date of follow-up for the first part of the study (RSA and DXA): February 28, 2023.

Finnish date of follow-up for all 122 patients: March 31, 2024.

## Data Availability

The electronic data will be stored in closed drives and printed data will be stored in closed cabinets. The datasets used and/or analyzed during the current study are available from the corresponding author on reasonable request.

## Abbreviations

RSA: Radiostereometric analysis
BMD: Bone mineral density
DXA: Duel energy x-ray absorptiometry
MB-RSA: Model-based radiostereometric analysis
WOOS: Western Ontario Osteoarthritis of the Shoulder index
OSS: Oxford Shoulder Score
ADL: Activities of daily living
VAS: Visual analogue scale
QALY: Quality-adjusted life year
SD: Standard deviation
MTPM: Maximum total point motion
